### Endpoints

#### Primary endpoint

The primary endpoint of the study is the mean change in HbA1c from baseline until 24 months later. We considered a change in HbA1c of 0.4 percentage points to be clinically significant [40]. In addition to the measurements at baseline and at 24 months, HbA1c is also measured at 3, 6, 12, and 18 months (Table 1).

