#### Statistical methods

Generalized linear mixed models with repeated time measurements will be used to analyze changes in outcomes over time. To compare the three interventions and the control group after different follow-up periods (Baseline, 3, 6, 12, 18, and 24 months), the intervention groups will be treated as a ‘factor within.’ First, we will examine whether the intervention in Groups 1 and 2 are better than usual care, and then, we will examine whether the most intensive intervention (group 3) is better than less intensive interventions (groups 1 and 2). The purpose of these analyses is to obtain preliminary estimates regarding the incremental benefits of the intervention components [45]. For multiple comparisons, the *P* value will be adjusted with Bonferroni correction (Pc Z corrected value). In addition, the models will include a subset of covariates that are imbalanced at baseline. To identify the covariates to be included in the model, we will first fit separate models including each covariate, one at a time. The final model will include those covariates such that their inclusion changes the estimates’ treatment effect by at least 10%. As suggested in the CONSORT statement, decisions about covariates will not be based on *P* value [46,47].

To incorporate the effect of cluster analysis, a multilevel model (MLM) approach will be implemented. MLM adjusts for the clustering effects across three levels (patients, FCU, and PHCP) of the hierarchical data structure.

For the main intention-to-treat analysis comparing outcomes, all patients will be included. Standard imputation methods (i.e., mean value imputation, last observation carried forward) will be used to impute missing data depending on the pattern of missing data. All tests will be two-sided with a type I error of 5%. Statistical analyses will be performed using Statistical Package for social Sciences (SPSS v.21, Chicago, IL, USA).

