##### Sample size calculation

We estimated that 393 patients per arm (total in the study = 1,572) were needed to detect an absolute difference in Hba1c of 0.4%, assuming a common standard deviation of 1.4% [40], a two-tailed power of 90%, and an alpha of 0.05. After an additional adjustment for clustering of patients within FCU by the design effect [48], assuming 15 patients per FCU and an intra-class correlation coefficient of 0.01 (interquartile range: 0 to 0.032) based on data from the literature [49], the estimated number of patients per arm was 448 (total in the study = 1,792). Although the unit of allocation was the PHCPs, these are formed of several healthcare centers throughout the territory that only share administrative management and some services. Also, this effect was already controlled by means of the stratification. Therefore, we considered that the intra-class correlation within PHCP was insignificant, and we used instead the intra-class correlation for FCU, that is, among patients served by the same FCU. Although small, we consider that this correlation is significant.

However, sample size was increased by an additional 30% to accommodate for expected losses to follow-up and to warrant the presence of each arm in the study in the different islands. Hence, we aimed for a total sample size of 2,330.

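### Covariates for the primary model are picked by observed imbalance and by how far they move the treatment effect, so the adjustment set depends on the result and baseline HbA1c is not guaranteed a place as a covariate

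*Protocol article*

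**What the plan says.** The protocol's Statistical methods section sets out a selection rule in three steps.

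- Imbalance: "the models will include a subset of covariates that are imbalanced at baseline".
- Single-covariate fits: "we will first fit separate models including each covariate, one at a time".
- Change in estimate: "The final model will include those covariates such that their inclusion changes the estimates’ treatment effect by at least 10" per cent.

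It adds a safeguard: "As suggested in the CONSORT statement, decisions about covariates will not be based on" the P value. It gives no list of candidates, no threshold for imbalance, and no covariate that is always included.

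Two other statements bear on baseline HbA1c. Under Primary endpoint: "The primary endpoint of the study is the mean change in HbA1c from baseline until 24 months later". And the repeated-measures comparison of the arms is made "after different follow-up periods (Baseline, 3, 6, 12, 18, and 24 months"), so baseline is one of the analysed time points. Whether the baseline mean is held equal across arms is not stated.

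The same section plans several arm contrasts: Groups 1 and 2 against usual care, then Group 3 against Groups 1 and 2. The Discussion describes the primary analysis as usual care against the three intervention groups.

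**The concern.** Change-in-estimate selection is a tool for finding confounders in observational data. In a randomised comparison, differences between arms at baseline arise by chance, and the reason to adjust is precision. What matters for that is how strongly a covariate predicts the outcome, not how far it happens to be out of balance.

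Three consequences follow.

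1. The selection statistic is the treatment effect itself. The same covariate in the same design enters or leaves according to how large the estimated effect is.
2. A strongly prognostic covariate that is well balanced is discarded by the imbalance step, and again by the 10% step, although it would narrow the confidence interval.
3. With several arm contrasts, a covariate can pass 10% for one and fail for another. The text does not say which contrast governs, so the choice would be made with results in view.

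At stake are the prespecification of the primary estimate and part of its precision.

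**Working it through.** The protocol gives no figure for this rule, so the check asks how often it would leave out the most obvious prognostic covariate, baseline HbA1c, and at what cost.

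**Inputs from the protocol (Sample size calculation).** Target difference 0.4, SD 1.4, 15 patients per FCU, ICC 0.01, two-sided alpha 0.05. Design effect: 1 + (15 − 1) × 0.01 = 1.14. This reproduces the stated step from 393 to 393 × 1.14 = 448 per arm. (The usual two-mean formula gives 258, not 393, from the stated inputs. That is a separate matter and does not affect this point.)

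**Assumed.** Baseline to 24-month correlation r = 0.5, with 0.3 and 0.7 as a range; imbalance read as a standardised difference above 0.1. The protocol gives neither. The check uses one two-arm contrast.

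**Formulas.** Let D0 and D1 be the between-arm differences at baseline and 24 months. Each has standard error s = 1.4 × √(2 × 1.14 / 448) = 0.0999.

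- Unadjusted change score: U = D1 − D0, SE = s√(2(1 − r)) = 0.100 at r = 0.5.
- Adjusted for baseline: A = D1 − rD0, SE = s√(1 − r²) = 0.086 at r = 0.5.
- Shift caused by adjustment: A − U = (1 − r)D0.

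So the 10% step keeps baseline HbA1c only if (1 − r)|D0| ≥ 0.1|U|.

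**By hand at r = 0.5.** If U is near 0.4, the step needs |D0| ≥ 0.04 / 0.5 = 0.08, which is 0.80 s. The chance of that is about 42%, so baseline is left out in about 58% of trials. If U is near 0.2, it needs |D0| ≥ 0.04, or 0.40 s, and baseline is left out in about 31%. The imbalance step needs |D0| > 0.1 × 1.4 = 0.14, or 1.40 s, which fails in about 84% of trials whatever the true effect.

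**Simulation of D0 and D1, r = 0.5** (allows for sampling variation in U):

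| True effect | Left out, 10% step | Left out, both steps | Rejects: unadjusted | 10% step | Both steps | Fixed adjustment |
|---|---|---|---|---|---|---|
| 0 | 11% | 84% | 5.0% | 4.3% | 3.9% | 5.0% |
| 0.2 | 31% | 84% | 52% | 60% | 54% | 64% |
| 0.4 | 57% | 84% | 98.0% | 99.5% | 98.8% | 99.6% |

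**Range over r.** At a true effect of 0.4, the 10% step alone leaves baseline out in 43% of trials at r = 0.3 and 81% at r = 0.7. At a true effect of 0.2, power under the 10% step, both steps and fixed adjustment is 51%, 41% and 55% at r = 0.3, and 78%, 75% and 80% at r = 0.7. With no effect, rejection stays below 5% under either version of the rule.

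If the 24-month value replaces the change score, the shift is −rD0. The drop rates at r = 0.5 are then the same; at r = 0.7 and a true effect of 0.4 the figure is 44%.

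**The case against.** Several counter-arguments are sound.

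- **The loss is modest.** The 10% step keeps baseline when it matters most to the estimate and so recovers much of the gain. At 0.4 the difference from fixed adjustment is negligible here. With clustering put at practice level (8 practices per arm, 56 patients each, ICC 0.01, r = 0.4), power is 92% under the 10% step and 94% with fixed adjustment. This stands, and it sets the size of the point.
- **Never adjusting is the wrong comparator.** The variance ratio (1 − r²) / (2(1 − r)) gives a 25% reduction at r = 0.5, but against a plan that never adjusts, which this one is not. Nor is planned precision lost: the sample size rests on a raw SD of 1.4 with no credit for baseline adjustment.
- **Analysis is blinded** (Blinding section). Masking limits deliberate steering. It does not stop the rule from using the contrast, which is visible under masked labels. Avoiding P values fails as a cure for the same reason.
- **An analysis plan may fill in details.** It may name candidates and thresholds, and their absence is not the complaint. The selection rule itself is stated in the protocol.

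Some stronger readings are tempting but unsupported. A reader might infer false-positive inflation; applied mechanically, the rule is slightly conservative. A reader might infer that baseline HbA1c disappears from the analysis; it remains in the change endpoint and as a repeated time point, and the drop rates concern only its role as a covariate. Nor does almost any noise covariate get in when the effect is near zero: a pure-noise covariate passes the 10% step in about 16% of null trials. The follow-up visits do not blur the target either, since the primary time point is fixed at 24 months; only the arm contrasts leave it open.

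**Conclusion.** The point holds in a limited form. The stated rule makes the adjustment set depend on observed imbalance and on the estimated treatment effect, allows it to differ between contrasts, and excludes balanced prognostic covariates.

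For baseline HbA1c the effect on selection is large. The effect on power is modest: at a true effect of 0.2 and r = 0.5, about 3 to 4 points for the 10% step alone and about 10 points if imbalance is also required. These sizes rest on the assumed correlation, the assumed imbalance threshold, a single two-arm change-score contrast and the protocol's own design effect.

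If baseline is modelled as a response with a common mean across arms, the precision loss for HbA1c disappears. The result-dependence of the rest of the adjustment set does not. The main ground for change is therefore prespecification, with precision second; the validity of the test is not in question.

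**What to change.** In the primary model, replace the imbalance and 10% rules by covariates fixed before unblinding and included whatever the imbalance or change in estimate:

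- baseline HbA1c, either as a covariate or as a common baseline mean in the repeated-measures model, stating which;
- the randomisation strata (island, and area within Tenerife and Gran Canaria).

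Use the same set for every arm contrast. Adjust each secondary outcome for its own baseline value where one is measured. Keep the imbalance and 10% rule, if wanted, as a labelled sensitivity analysis.

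The cost is wording only. HbA1c is measured at baseline and stratum is known for every practice, so no new data or patients are needed. The trial is described as ongoing, so the change can be made before the outcome data are unblinded.

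### Missing outcomes in the main analysis are to be filled by mean imputation or LOCF, although the planned repeated-measures model can use all observed HbA1c values without imputation

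*Protocol article*

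**What the plan says.** The protocol article, Primary endpoint, states: "The primary endpoint of the study is the mean change in HbA1c from baseline until 24 months later". It adds that "HbA1c is also measured at 3, 6, 12, and 18 months", so each patient has up to six HbA1c values.

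Under Statistical methods the model is described as follows: "Generalized linear mixed models with repeated time measurements will be used to analyze changes in outcomes over time". Baseline is listed among the time points compared, and a multilevel structure of patients, FCUs and PHCPs is specified. Tests are two-sided at 5%.

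The same section covers the analysis set and missing values: "For the main intention-to-treat analysis comparing outcomes, all patients will be included", followed by "Standard imputation methods (i.e., mean value imputation, last observation carried forward) will be used to impute missing data", with the choice made according to the missingness pattern.

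Under Sample size calculation, "sample size was increased by an additional 30% to accommodate for expected losses to follow-up". That sentence goes on to give a second purpose for the increase: securing the presence of every arm on the different islands. No attrition rate is given. The article names no multiple imputation and no sensitivity analysis for missing data.

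**The concern.** Both named methods put one invented value in each gap and then treat it as measured. Mean imputation places the missing patients exactly at an average, which removes their variation. LOCF takes an earlier HbA1c as the 24-month result; for a patient seen only at baseline, that means a change of exactly zero.

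Neither step is needed. A mixed model fitted by likelihood to the observed visits keeps every patient with at least one HbA1c value, so it serves the intention-to-treat aim. It is valid under missing at random if its mean and covariance structures are right. Filling the gaps first gives up that property.

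At stake are the size of the primary 24-month contrast and, depending on the variant used, the stated 5% error rate. The trial is open, and groups 1 and 3 carry a burden (eight 3-hour sessions, workbooks, weekly web entry) that usual care does not. Unequal loss is therefore plausible, though the article does not document it.

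**Working it through.** **How much loss the plan allows for.** The later steps of the sample size reproduce:
- design effect 1 + (15 − 1) × 0.01 = 1.14; 393 × 1.14 = 448 per arm
- 448 × 4 = 1,792; 1,792 × 1.30 = 2,330, about 583 per arm
- largest loss absorbed: 1 − 1,792/2,330 = 23.1%

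The starting figure of 393 does not follow from a difference of 0.4, SD 1.4, 90% power and two-sided 5%, which give 258 per arm. That is a separate matter and does not enter the results below. The 23.1% is a ceiling and not a forecast, so a range of p is shown.

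**Mean taken within arm.** Take n per arm, a fraction p missing completely at random in each arm, and no clustering or covariates.
- True SE = SD × √(2 / [n(1−p)])
- After filling, the SD shrinks to SD × √(1−p) and n is counted as full: model SE = SD × √(1−p) × √(2/n)
- Ratio of model SE to true SE = 1 − p
- Example with SD 1.4, n = 583, p = 0.231: true SE = 1.4 × √(2/448.3) = 0.0935; model SE = 1.4 × 0.877 × √(2/583) = 0.0719; ratio 0.769
- Actual type I error = 2 × [1 − Φ(1.96 × (1−p))]

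| p | Model SE / true SE | Type I error, arm mean | 0.40 effect, pooled mean |
|---|---|---|---|
| 10% | 0.90 | 7.8% | 0.36 |
| 20% | 0.80 | 11.7% | 0.32 |
| 23.1% | 0.769 | 13.2% | 0.31 |

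**Mean pooled over arms.** With equal loss, the estimate and its model SE both shrink by about (1−p), so the test statistic is essentially that of the complete cases. A simulation of 20,000 null trials (583 per arm, 23.1% missing in each arm) gave a type I error of 4.9%. The harm is to the estimate: 0.40 × (1 − 0.231) = 0.31.

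**LOCF.** These two scenarios are assumed, to show that the direction is open:
- 30% leave right after baseline and the true effect is 0.40: 0.70 × 0.40 + 0.30 × 0 = 0.28, too small
- 25% leave at month 6, with an effect of 0.6 then and 0.3 at month 24: 0.75 × 0.3 + 0.25 × 0.6 = 0.375 against a true 0.30, too large

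**Simulation of two arms.** Settings: 583 per arm, six visits, SD 1.4, 1,500 runs per scenario, no clustering, 24-month value adjusted for baseline. Visit correlation, dropout mechanism and linear build-up of effect and drift are assumptions.
- True effect −0.40, 23% missing completely at random in both arms: LOCF −0.337 with 79% coverage of the 95% interval. Arm mean −0.400, but model SE 0.056 against an actual 0.075, with 86% coverage. The likelihood-type estimate from the observed visits is −0.40 with SE 0.064.
- No effect, upward drift of 0.4, 15% against 30% missing completely at random: type I error 12% for LOCF and 13% for arm mean.
- No effect, drift of 0.4 up or down, dropout depending on the last HbA1c, 16–17% against 31–33% missing: LOCF bias −0.03 to +0.06 with type I error 9–20%; arm-mean bias about −0.1 with type I error 42–47%.
- In these null scenarios the likelihood-type estimate stays at 0.00.

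**The case against.** A reader might infer that single imputation as such understates the standard error and pushes the type I error above 5%. The article does not support that in general. It does not say whether the mean is taken within arm or over all patients, and the 13% belongs to the within-arm version only. For LOCF, the model SE matched LOCF's own spread (0.054 each). A null simulation without drift (8,000 runs) gave a type I error of 5.0%, both with 23% missing in each arm and with 15% against 30%. LOCF does its harm mainly through bias.

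A reader might also take the sample-size increase as a forecast of 23% or 30% loss. It is neither. The increase also serves the distribution of arms over the islands, no attrition rate is given, and 30% missing has no support in the document. At 10% missing, even the within-arm version reaches only 7.8%.

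It is also fair to say that the choice of method is tied to the pattern of missing data, and that filling before modelling is the natural reading but not an explicit statement.

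What does not stand is the reply that this is a detail for an unseen analysis plan. The article defines its standard methods as these two, and the clause on pattern only chooses between them.

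**Conclusion.** The point holds in this form: the article fixes single imputation for the main analysis although its own model makes imputation of HbA1c unnecessary, and neither stated method is generally valid.

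- **Within-arm mean:** actual type I error of about 8%, 12% and 13% at 10%, 20% and 23.1% missing, assuming missing completely at random, no clustering and every missing 24-month value mean-filled.
- **Pooled mean:** error rate near 5% under equal loss, but the effect is diluted, from 0.40 to about 0.31 at 23.1%.
- **LOCF:** a biased 24-month contrast whose size and sign cannot be determined from the document; the LOCF figures above are illustrations.

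That the method is poorly chosen is certain from the text. How much it matters depends on an attrition rate and a dropout pattern that the article does not give.

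**What to change.** - Drop mean imputation and LOCF from the primary analysis. Fit the planned multilevel repeated-measures model by likelihood to all observed HbA1c values of all enrolled patients, analysed by the allocation of their PHCP, and state the missing-at-random assumption.
- Where completed data are needed (QALYs, costs, questionnaire scores), use multiple imputation that respects arm and clustering.
- Add a sensitivity analysis for HbA1c data missing not at random. LOCF may remain only as a secondary sensitivity analysis.

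The cost is a change of wording and a little more analysis work, with no new patients, visits or measurements. The article reports recruitment complete and the trial ongoing, so the change should be recorded before the outcome data are analysed.

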##### Sample size calculation

We estimated that 393 patients per arm (total in the study = 1,572) were needed to detect an absolute difference in Hba1c of 0.4%, assuming a common standard deviation of 1.4% [40], a two-tailed power of 90%, and an alpha of 0.05. After an additional adjustment for clustering of patients within FCU by the design effect [48], assuming 15 patients per FCU and an intra-class correlation coefficient of 0.01 (interquartile range: 0 to 0.032) based on data from the literature [49], the estimated number of patients per arm was 448 (total in the study = 1,792). Although the unit of allocation was the PHCPs, these are formed of several healthcare centers throughout the territory that only share administrative management and some services. Also, this effect was already controlled by means of the stratification. Therefore, we considered that the intra-class correlation within PHCP was insignificant, and we used instead the intra-class correlation for FCU, that is, among patients served by the same FCU. Although small, we consider that this correlation is significant.

However, sample size was increased by an additional 30% to accommodate for expected losses to follow-up and to warrant the presence of each arm in the study in the different islands. Hence, we aimed for a total sample size of 2,330.

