**Methods/design:**

The INDICA study is an open, community-based, multicenter, clinical controlled trial with random allocation by clusters to one of three interventions or to usual care. The setting is primary care where physicians and nurses are invited to participate. Patients with diabetes diagnosis, 18–65 years of age, and regular users of mobile phone were randomly selected. Patients with severe comorbidities were excluded. The clusters are primary healthcare practices with enough professionals and available places to provide the intervention. The calculated sample size was 2,300 patients.

Patients in group 1 are receiving an educational group program of eight sessions every 3 months led by trained nurses and monitored by means of logs and a web-based platform and tailored semi-automated SMS for continuous support. Primary care professionals in group 2 are receiving a short educational program to update their diabetes knowledge, which includes a decision support tool embedded into the electronic clinical record and a monthly feedback report of patients’ results. Group 3 is receiving a combination of the interventions for patients and professionals.

The primary endpoint is the change in HbA1c in 2 years. Secondary endpoints are cardiovascular risk factors, macrovascular and microvascular diabetes complications, quality of life, psychological outcomes, diabetes knowledge, and healthcare utilization. Data is being collected from interviews, questionnaires, clinical examinations, and records. Generalized linear mixed models with repeated time measurements will be used to analyze changes in outcomes.

The cost-effectiveness analysis, from the healthcare services perspective, involves direct medical costs per quality-adjusted life year gained and two periods, a ‘within-trial’ period and a lifetime Markov model. Deterministic and probabilistic sensitivity analyses are planned.

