### Setting and recruitment

PHCP were randomly recruited in four of the seven Canary Islands (Tenerife, Gran Canaria, Lanzarote, and La Palma). Tenerife and Gran Canaria are the main and most populated islands, providing 12 PHCP each (four from metropolitan areas, four from the south, and four from the north). La Palma and Lanzarote are less populated islands and provided four PHCP each. The Human Resources Department of the CIHS at every island supplied us with an updated list of publicly available physician/nurses for every selected PHCP. FCUs’ recruitment in PHCPs was supported by informative meetings preceded by meetings with local health authorities as well as with the directors of all selected PHCP on every island. In these meetings, a 60–80-min presentation describing the study objectives, planned time frame and tasks to be developed by healthcare professionals, expected resources utilization, and funding procedures were detailed.

After FCUs agreed and consented to participate, the electronic clinical records (ECR) of all potentially eligible patients in the selected FCU were screened to verify all inclusion and exclusion criteria. Once identified, patients received a phone call to explain the study objectives, informing that they might be eligible to participate and inviting them to an initial meeting in their respective PHCP. In this meeting, the study staff provided face-to-face extended information about the study, confirmed patient eligibility, and invited them to sign individual patient informed consent.

When a participant physician/nurse left their practice, they were excluded from the study and replaced by the new physician/nurse. In groups 2 and 3, the educational intervention was given to the new healthcare professionals on an individual level. Their corresponding patients were kept in the study without changes.

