### Random assignment

Randomization was applied at different levels in every island included in the trial. Three different strata or geographic areas were set in Tenerife and Gran Canaria (metropolitan, northern, and southern areas). Four PHCP were randomly allocated to every stratum. Each PHCP was assigned to one of the three interventions or control arms by block permutation. La Palma and Lanzarote were geographically divided into four zones with only one PHCP available in each zone. Each of these PHCP was randomly assigned to one of the study arms. In every island, all arms were equally distributed.

Six FCUs were randomly selected from all those consenting participants at each PHCP. From all patients fulfilling inclusion criteria and consenting to participate in each PHCP, 15 were randomly selected per FCU. Exceptionally, more than six FCUs or more than 15 patients per FCU were selected, in order to recruit 90 patients at every PHCP.

While PHCP randomization was performed using block permutation at three different levels, second (FCUs) and third (patients) stage randomizations were performed by simple generation from a list of random numbers. PHCP assignment to interventions or control group was performed by the data manager.

In order to prevent potential contamination among study interventions, all FCUs at every PHCP were allocated to the same study group.

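### The base sample size of 393 per arm does not follow from the stated inputs, which give 258; either 393 or the printed SD and power is misreported

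*Protocol article*

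**What the plan says.** The section on sample size calculation in the Protocol article opens with the base figure: "We estimated that 393 patients per arm (total in the study = 1,572) were needed to detect an absolute difference". The difference is given as an "absolute difference in Hba1c of 0.4" percentage points, and the remaining inputs as "assuming a common standard deviation of 1.4% [40], a two-tailed power of 90%, and an alpha of 0.05". The section then applies a design effect for 15 patients per Family Care Unit (FCU) with an intra-class correlation of 0.01, reaching 448 per arm and 1,792 in all. It adds 30% and concludes that "we aimed for a total sample size of 2,330".

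The abstract, under Methods/design, has: "The calculated sample size was 2,300 patients".

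The recruitment sections describe a field quota. Tenerife and Gran Canaria are described as "providing 12 PHCP each (four from metropolitan areas, four from the south, and four from the north"), and La Palma and Lanzarote contribute four primary healthcare practices (PHCPs) each. Within each PHCP, six FCUs with 15 patients each are drawn, with exceptions allowed "in order to recruit 90 patients at every PHCP".

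Two other statements bear on the inputs. The Statistical methods section makes all tests two-sided at 5%. The Random assignment section says the arms are equally distributed on every island.

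**The concern.** The article prints every input to a standard two-group comparison of means, together with the result, and the two disagree by about half. This is not a detail that a condensed article leaves to a fuller document.

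What is at stake is the stated power for the primary endpoint, and the direction of the error is unknown. If the SD and power are right and 393 is wrong, the trial has more power than it claims at this step. If 393 came from a larger SD or a lower power, the reported 90% overstates what the trial was sized for. The results will be read against this statement, and a reader cannot tell which case applies.

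A smaller question sits beside it: how the calculated total relates to the number that the recruitment scheme would produce.

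**Working it through.** **Inputs.** Difference d = 0.4, SD s = 1.4, power 90%, alpha 0.05 (Sample size calculation); two-sided tests (Statistical methods); four equal arms (Random assignment).

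**Step 1: the base figure from the stated inputs.**
n per arm = 2 × (z₀.₉₇₅ + z₀.₉₀)² × (s/d)²
= 2 × (1.960 + 1.2816)² × (1.4/0.4)²
= 2 × 10.507 × 12.25 = 257.4, so 258 per arm and 4 × 258 = 1,032 in all. The exact t-test solution is 258.4, so 259.
The plan's 393 is not reproduced: 393/258 = 1.52.

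**Step 2: power at 393 per arm.**
√(393/2) × 0.4/1.4 = 4.005, and 4.005 − 1.960 = 2.045, which gives power of 0.980.

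**Step 3: the plan's later figures.**
- Design effect: 1 + (15 − 1) × 0.01 = 1.14
- 393 × 1.14 = 448.0
- 448 × 4 = 1,792
- 1,792 × 1.3 = 2,329.6, rounded to 2,330

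These reproduce, so only the base figure fails.

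**Step 4: could multiplicity explain 393?** The sample size section states alpha 0.05, but Statistical methods mentions Bonferroni. With SD 1.4 and 90% power:

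| Scheme | n per arm |
|---|---|
| 3 comparisons (each intervention against control) | 331 |
| 4 comparisons (groups 1 and 2 against control, then 3 against 1 and 2) | 350 |
| 6 comparisons (all pairs) | 377 |
| 7 comparisons | 387 |
| 8 comparisons | 396 |
| Four-group ANOVA, extreme means 0.4 apart | 349 |
| Tukey | 364 |
| Scheffé | 408 |

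Seven and eight comparisons bracket 393, but the article describes no scheme with that many.

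**Step 5: which unstated inputs would give 393?**
- Changing one input at a time: SD 1.73, or a difference of 0.324, or alpha of about 0.0065, or power of 98%.
- Changing SD and power together: 2 × (1.960 + 0.8416)² × (2.0/0.4)² = 392.4, so 393. SD 2.0 with 80% power therefore gives the printed figure exactly.
- Counting adjustments in the base: 258 × 1.14/0.75 = 392.2, which is 393 if rounded up. This would put the design effect and a 25% loss inside a figure that the article presents as coming before both.

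More than one route reaches 393, so numerical agreement does not identify the source.

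**Step 6: the chain on the stated inputs.**
- 258 × 1.14 = 294.1, so 295 per arm
- 295 × 4 = 1,180
- 1,180 × 1.3 = 1,534

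**Step 7: the recruitment quota.**
12 + 12 + 4 + 4 = 32 PHCPs, and 32 × 90 = 2,880. That is 24% above 2,330 (2,880/2,330 = 1.236). Spread evenly, 2,330 would be about 73 per PHCP (2,330/32 = 72.8).

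**The case against.** The strongest reply is that the error is harmless. On the stated inputs 393 is more than enough: it gives 98% power and exceeds the need under three, four or all six Bonferroni comparisons (331, 350, 377). Recruitment is complete, and no estimand, test or analysis depends on the figure. This holds if the printed SD and power are the true assumptions, and the article gives no way to confirm that. If SD 2.0 and 80% power were used, the trial was sized for 80%, and 90% at that SD would have needed 2 × 10.507 × 25 = 525.4, so 526 per arm before clustering.

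A reader might infer more than the article supports in four places:

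- **That the trial is definitely oversized, or definitely underpowered.** Neither follows. SD 2.0 with 80% power is a reconstruction, and so is the assumption that only 393 is wrong.
- **That 2,330, 2,300 and 2,880 are three conflicting versions of one number.** The 2,300 is 1.3% below 2,330 and may be rounding. The 2,880 is printed nowhere. It is what the field quota implies, and a quota above a calculated requirement is not a contradiction. What remains fair is that the article never relates the two.
- **That the 30% step is wrong because losses call for division by 0.7.** The article gives the 30% two purposes, follow-up losses and having every arm present on the islands. It does not say that 30% loss is expected.
- **That the excess conceals neglected clustering by PHCP.** The section raises that clustering openly and gives reasons for treating it as negligible. Those reasons can be debated separately.

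**Conclusion.** The statement is wrong as printed. A difference of 0.4, SD 1.4, 90% power and two-sided alpha 0.05 give 258 per arm (1,032), not 393 (1,572). The gap is 135 per arm, or 52%, and the 448, 1,792 and 2,330 built on it carry the same inconsistency. This rests only on figures in the article, with equal arms and the usual two-sample formula. No multiplicity scheme that the article describes closes the gap.

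The article does not show which element is misreported. It may be the base figure, or the SD, the power or both. The stated 90% power for the primary endpoint therefore cannot be relied on until the authors say which inputs were used. The point concerns the reported calculation. It does not show that the trial enrolled too few or too many patients.

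**What to change.** 1. State the SD, power and alpha that actually produced 393. If the printed inputs were the intended ones, correct the chain instead: 258 per arm, 295 after the design effect of 1.14, 1,180 in total and about 1,534 with the added 30%.
2. Report the power for a 0.4 difference with the number actually recruited, at the alpha and clustering structure used in the analysis.
3. Add one sentence relating the calculated 2,330 to the quota of 90 patients at each of 32 PHCPs (2,880), and bring the abstract's 2,300 into line or mark it as rounded. The quota should not replace the calculated requirement.

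The cost is a rewrite of the sample size section, one sentence on recruitment and one figure in the abstract. The Trial status section says that recruitment is complete, so enrolment does not change.
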